#### **6.2.6 Visit 1: Month 1**

- Vital signs
- Physical exploration
- Blood sampling for routine laboratory testing
- Urinalysis
- Pain assessment of the lumbar spine by visual pain scale (VAS)
- Oswestry Disability Index in order to measure a patient's permanent functional disability, Quality of life assessment using SF-36
- Adverse event assessment
- Instruction for wash out (NSAIDS washout of at least 2 days before this Visit, no painkillers 24h before the visit)
- Prohibition of NSAIDs
- Concomitant medication

#### **6.2.7 Visit 2: Month 3**

- Blood sampling for routine laboratory testing
- Urinalysis
- Pain assessment of the lumbar spine by visual pain scale (VAS)

- Oswestry Disability Index in order to measure a patient's permanent functional disability, Quality of life assessment using SF-36
- Adverse event assessment
- Instruction for wash out (NSAIDS washout of at least 2 days before this Visit, no painkillers 24h before the visit)
- Prohibition of NSAIDs
- Concomitant medication

#### **6.2.8 Visit 3: Month 6**

- Vital signs
- Physical exploration
- Blood sampling for routine laboratory testing
- Urinalysis
- Lateral MRI, T2, quantitative
- Pain assessment of the lumbar spine by visual pain scale (VAS)
- Oswestry Disability Index in order to measure a patient's permanent functional disability, Quality of life assessment using SF-36
- Adverse event assessment
- Concomitant medication
- Instruction for wash out (NSAIDS washout of at least 2 days before this Visit, no painkillers 24h before the visit)
- Prohibition of NSAIDs

#### **6.2.9 Visit 4: Month 12**

- Vital signs
- Physical exploration
- Blood sampling for routine laboratory testing
- Urinalysis
- Lateral MRI, T2, quantitative
- Pain assessment of the lumbar spine by visual pain scale (VAS)
- Oswestry Disability Index in order to measure a patient's permanent functional disability, Quality of life assessment using SF-36
- Adverse event assessment

- Concomitant medication
- Instruction for wash out (NSAIDS washout of at least 2 days before this Visit, no painkillers 24h before the visit)
- Prohibition of NSAIDsa

#### **6.2.10 Visit 5: Month 24**

- Vital signs
- Physical exploration
- Blood sampling for routine laboratory testing
- Urinalysis
- Lateral MRI, T2, quantitative
- Pain assessment of the lumbar spine by visual pain scale (VAS)
- Oswestry Disability Index in order to measure a patient's permanent functional disability, Quality of life assessment using SF-36
- Adverse event assessment
- Concomitant medication
- Instruction for wash out (NSAIDS washout of at least 2 days before this Visit, no painkillers 24h before the visit)
- Prohibition of NSAIDsa

### **6.3 Unscheduled visits**

If subject gets in contact with the site between regular visits due to acute disorders, an unscheduled visit will promptly be performed at the site. During this additional visit a physical examination, a systematic interview for recording AEs should be performed. In case of suspected local infection (nocturn lumbar pain, temperature above 38°C), disc puncture will be performed and an empirical antibiotic treatment will be initiated immediately and further tuned according to the antibiogram

### **6.4 Concomitant therapy and Rescue therapy**

Rehabilitation: Lifestyle modification, particularly exercise and weight reduction, is a core component of the management of low back pain.

Rescue medication use will be recorded for the study duration. Within 24 hours following MSC injection, paracetamol/acetaminophen will be advised for each patient if needed.

Patients will be required to refrain from taking paracetamol or opioids within 24 hours of each clinical visit for efficacy evaluations. If the patient required, supplementary analgesic medication will be provided. Tramadol will be used as rescue medication.

NSAIDs will not be authorized during the first 6-month of the study. However, if needed after the first 6 months, NSAIDs could be used.

A diary file will be provided for each patient in order to collect information on medications use, mobility, activities and rehabilitation sessions.

## **6.5 Contraceptive methods**

Adult subjects of childbearing potential (ACBP) must:

- Understand the potential teratogenic risk to the unborn child and the need for effective contraception.
- Be capable of complying with effective contraceptive measures.
- Be informed and understand the potential consequences of pregnancy and the need to notify her study doctor immediately if there is a risk of pregnancy.
- Understand the need to commence the study treatment as soon as study drug is dispensed following a negative pregnancy test.
- Understand the need and accept to undergo pregnancy testing based on the frequency outlined in this protocol.
- ACBP enrolled in this protocol must agree to use two reliable forms of contraception simultaneously or to practice complete abstinence from heterosexual contact during the following time periods related to this study: 1) while participating in the study; 2) in case of dose interruptions; and 3) for at least 24 months after the last dose of study drug.
- The two methods of reliable contraception must include one highly effective method and one additional effective (barrier) method. ACBP must be referred to a qualified provider of contraceptive methods if needed. The following are examples of highly effective and additional effective methods of contraception.

### **Highly effective methods:**

- \*Hormonal (birth control pills, injections, implants)
- Tubal ligation
- Partner's vasectomy (if medical assessment ascertain the surgical success)
- Intrauterine Device (IUD)
- Intrauterine hormone-releasing system (IUS)

- Bilateral tubal occlusion
- Sexual abstinence (if defined as refraining from heterosexual intercourse during the entire period of risk associated with the study treatments. The reliability of sexual abstinence needs to be evaluated in relation to the duration of the clinical trial and the preferred and usual lifestyle of the subject.)

**-Additional effective methods:**

- Male condom
- Diaphragm (not recommended in patients with low platelets count)
- Cervical cap.

**Males with ACBP Partners:**

- Condom
- Contraception during treatment and until the end of relevant systemic exposure in ACBP.

**Definition:**

Women of childbearing potential a woman is considered of childbearing potential (WOCBP), i.e. fertile, following menarche and until becoming post-menopausal unless permanently sterile. Permanent sterilisation methods include hysterectomy, bilateral salpingectomy and bilateral oophorectomy.

A postmenopausal state is defined as no menses for 12 months without an alternative medical cause. A high follicle stimulating hormone (FSH) level in the postmenopausal range may be used to confirm a post-menopausal state in women not using hormonal contraception or hormonal replacement therapy. However in the absence of 12 months of amenorrhea, a single FSH measurement is insufficient.

A man is considered fertile after puberty unless permanently sterile by bilateral orchidectomy.

## **7. Statistic analysis planning and power calculation**

Sample size was calculated to have 80% power and 2 balanced groups and according to the literature data (Maher et al., 2017; PopulationReferenceBureau; 2016), a responder rate is expected at 12 months of the order of 30% in controls and 68% for MSC is a delta of 38% between the two groups. To highlight this

difference while justifying a power of 80% and an alpha risk of 5% and within 1:1 ratio, taking into account 20% of inclusion failure, it is necessary to include 26 individuals per group a total of 52 subjects.

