### **3.8 Replacement of patients**

Drop-outs will not be replaced (the sample size has been increased assuming a drop-out rate of 10%).

If a patient is withdrawn from the clinical trial before injection of the cells, it will be replaced by another eligible patient.

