### **7.1 Statistic analysis**

Evaluation of the treatment effect will be obtained with analysis of variance (ANOVA) and Student T test.

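### The stated 26 per arm does not contain the 20% loss allowance claimed for it under a two-sided 5% test, and Section 3.8 gives 10% instead

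*Protocol*

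**What the plan says.** Protocol Section 7 gives the planning assumptions: "a responder rate is expected at 12 months of the order of 30% in controls and 68% for MSC", with "a power of 80% and an alpha risk of 5% and within 1:1 ratio". From these it concludes: "taking into account 20% of inclusion failure, it is necessary to include 26 individuals per group a total of 52 subjects". The synopsis repeats the statement.

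Section 3.8 describes the allowance differently: "Drop-outs will not be replaced (the sample size has been increased assuming a drop-out rate of 10" per cent). Sections 3.5 and 3.8 both add that a patient withdrawn before the cells are injected is replaced.

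No section says whether the 5% is one- or two-sided, or which test the calculation refers to. For the analysis, Section 7.1 says: "Evaluation of the treatment effect will be obtained with analysis of variance (ANOVA) and Student T test".

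**The concern.** One sample size carries two different allowances, 20% and 10%, under two different labels: failure of inclusion and drop-out. The inputs are complete apart from sidedness, so the number can be checked. On the conventional two-sided reading the 20% cushion is not there, because 26 is what the formula returns with nothing added.

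At stake is how the result will be read. Section 1.6 presents the trial as one that will either support or refute the treatment. If the test is two-sided and 20% of patients are lost, the chance of missing the planned effect is about 24–30%, not 20%. A null result would then be given more weight than the design earns.

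**Working it through.** **Inputs (Protocol Section 7).** p1 = 0.30, p2 = 0.68, difference d = 0.38, mean p = 0.49, power 80% (z = 0.8416), alpha 5% (z = 1.960 two-sided, 1.645 one-sided), allocation 1:1. Loss allowance L = 20% (Section 7) or 10% (Section 3.8).

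**Number per arm before losses**

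- Pooled, two-sided: [1.960·√(2·0.49·0.51) + 0.8416·√(0.30·0.70 + 0.68·0.32)]² / 0.38² = (1.3856 + 0.5503)² / 0.1444 = 25.96, so 26.
- Unpooled, two-sided: (1.960 + 0.8416)² · (0.2100 + 0.2176) / 0.1444 = 23.24, so 24.
- Pooled, one-sided: (1.1629 + 0.5503)² / 0.1444 = 20.33, so 21.

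The plan's 26 therefore appears directly as the two-sided pooled number with no allowance.

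**With the allowance, n/(1 − L)**

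| Formula | Before losses | With 10% | With 20% |
|---|---|---|---|
| Pooled, two-sided | 25.96 | 28.8, so 29 | 32.4, so 33 |
| Unpooled, two-sided | 23.24 | 25.8, so 26 | 29.05, so 30 |
| Pooled, one-sided | 20.33 | 22.6, so 23 | 25.4, so 26 |

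Other two-sided variants do not rescue 26 with 20% included. The arcsine formula gives 33 and the continuity-corrected formula 39. Multiplying by 1.2 instead of dividing by 0.8 gives 32 (pooled, 25.96 × 1.2 = 31.1) or 28 (unpooled, 23.24 × 1.2 = 27.9). The two matches in the table also depend on rounding only at the end: 24/0.9 = 26.7 and 21/0.8 = 26.25 would each round to 27.

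**Power with 26 randomised per arm, two-sided 5%.** A 10% loss leaves 23.4 (taken as 23) and a 20% loss leaves 20.8 (taken as 21).

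- Pooled normal: Φ[(0.38·√n − 1.3856)/0.6539]. For n = 21 this is Φ[(1.7414 − 1.3856)/0.6539] = Φ(0.544) = 70.7%.
- Unpooled normal: Φ[0.38·√n/0.6539 − 1.960]. For n = 21 this is Φ(0.703) = 75.9%.
- Exact: the binomial probabilities of all tables that the test rejects are summed.

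| Analysed per arm | Pooled normal | Unpooled normal | Exact chi-square |
|---|---|---|---|
| 26 (no loss) | 80.1% | 84.2% | 78.5% |
| 23 (10% loss) | 74.8% | 79.6% | 76.6% |
| 21 (20% loss) | 70.7% | 75.9% | 70.0% |

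A Student t test on the 0/1 responder variable, enumerated the same way, gives 69.6% at 21 per arm. The lower end of the range thus also applies to a test that Section 7.1 names.

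**One-sided 5%.** With 21 analysed per arm, power is 81.2% (pooled normal) or 80.0% (exact chi-square).

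**The case against.** The strongest reply is that the protocol never says two-sided. With a one-sided 5% test, 26 including 20% reproduces and 21 analysed per arm gives about 80% power. That is correct, and it is why the point is conditional. It does not make the text adequate, since a one-sided 5% test is declared nowhere. The ANOVA F test in Section 7.1 has no direction, and for two groups it is equivalent to a two-sided t test. The t test also named there could be one-sided, so this is evidence about the intended reading and not proof.

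The second reply is that failure of inclusion need not mean drop-out. If it means screen failures or withdrawals before injection, the treated number stays at 26 per arm, because Sections 3.5 and 3.8 replace patients withdrawn before injection. Two-sided pooled power is then 80.1% with complete data. This too is fair, but 26 would then carry no margin in the pooled calculation for loss after injection, although Section 3.8 says such a margin was added.

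Third, the unpooled two-sided formula with 10% does give 26. On that reading Section 3.8 is consistent with the sample size, and the 20% in Section 7 and the synopsis is the mistake.

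Fourth, the loss calculation simply removes patients. Section 7.5 plans multiple imputation for data missing at random, and Section 1.7 counts a patient who has surgery for severe sciatica as a failure. Some lost patients will therefore still contribute. Imputation does not restore full information, so the figures for 21 and 23 per arm are approximations to the planned analysis, not properties of it.

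A reader might infer that the trial simply has 70% power instead of 80%. The documents do not support that. It requires a two-sided test, the full 20% taken as post-treatment loss, and the pooled, chi-square or t calculation.

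**Conclusion.** The statement is wrong or incomplete as written, whichever reading was intended. If the test is two-sided, 26 per arm does not give 80% power after 20% losses by any formula tried; that would take 30 to 33 per arm (60 to 66 in total) by the unpooled or pooled formula. If the test is one-sided, the protocol omits the fact on which the number depends. In both cases the 20% of Section 7 and the synopsis conflicts with the 10% of Section 3.8.

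The two-sided shortfall ranges from almost none (10% loss, unpooled) to about 10 percentage points (20% loss, pooled or exact). All figures rest on the protocol's own 30% and 68%. Exact power does not rise smoothly at these sizes (79.5% at 24 per arm, 78.5% at 26), so single exact values should not be read to the last point.

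**What to change.** Keep 52 patients and correct the wording in Section 7, Section 3.8 and the synopsis:

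- State whether the 5% is one- or two-sided, and name the test and formula behind the figure.
- Use one post-treatment drop-out rate throughout. Keep it separate from screen failures and from withdrawals before injection, which are replaced.
- Give the power with complete data and at that drop-out rate.
- If the test is two-sided, drop the claim that 26 per arm gives 80% power after 20% losses. The figures to report are about 80% with complete data by the pooled approximation (78.5% by exact chi-square), and about 75–80% at 10% loss or 70–76% at 20% loss, quoted for the one test and rate chosen.
- If the test is one-sided 5%, declare it and show the two-sided power beside it.

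The cost is a text amendment in three places and, if the test is two-sided, a less favourable stated power. It adds no patients and changes no procedure.

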### **7.1 Statistic analysis**

Evaluation of the treatment effect will be obtained with analysis of variance (ANOVA) and Student T test.

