## **2.4 Endpoints**

### **2.4.1 Primary Endpoint:**

- To evaluate the efficacy of intradiscal injection of autologous BM-MSC using the visual analog scale (VAS) and functional status assessed by the Oswestry disability index (ODI) after 24 months of treatment, defining

responders in case of at least 40% improvement in VAS or ODI at month 24 compared to baseline.

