## **4. Measurement of outcomes**

### **4.1 Primary Outcome Measures:**

The clinical response is defined as pain relief of at least 40% and 40 mm decrease on VAS scale between baseline and month 24, or 40% improvement of functional index ODI at month 24 compared to baseline. Chronic LBP is assessed using the VAS pain scale (0 – 100, where 0 represents no pain and 100 represents the worst pain imaginable). ODI scale ranges from 0 to 50 and allows evaluation of disability (0% – 20%: minimal disability; 20% – 40%: moderate disability; 40% – 60%: severe disability; 60% – 80%: crippled; 80% – 100%: bed-bound or exaggerating their symptoms).

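### Section 7.1 names only ANOVA and Student's t test without saying for which outcome, so the test of the responder endpoint on which the trial is sized is left undetermined

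*Protocol*

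**What the plan says.** - **Primary endpoint (Protocol 2.4.1).** Binary: "responders in case of at least 40% improvement in VAS or ODI at month 24 compared to baseline".
- **Primary outcome measure (Protocol 4.1).** Also binary, but with a different VAS rule: "The clinical response is defined as pain relief of at least 40% and 40 mm decrease on VAS scale between baseline and month 24", or a 40% improvement on ODI.
- **Sample size (Protocol 7).** Built on two proportions: "a responder rate is expected at 12 months of the order of 30% in controls and 68% for MSC", with "a power of 80% and an alpha risk of 5% and within 1:1 ratio" and "taking into account 20% of inclusion failure", giving 26 per group and 52 in total. Sidedness is not stated. No mean difference or standard deviation is given.
- **Analysis of the treatment effect (Protocol 7.1, complete).** "Evaluation of the treatment effect will be obtained with analysis of variance (ANOVA) and Student T test".
- **Sensitivity analysis (Protocol 7.2).** A worst-case scenario counts patients with missing data as non-responders in the cell arm and responders in the control arm. A multivariate regression of unspecified type checks covariates. No test is named for the responder comparison.
- **Continuous outcomes (Protocol 2.4.2).** ODI and SF-36 as continuous measures are secondary endpoints.
- **What is left to the SAP (Protocol 7.5).** Only the imputation rules are expressly deferred.

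**The concern.** ANOVA and Student's t test compare means. The endpoint, the power statement and the worst-case analysis all concern the proportion of responders. Section 7.1 fixes a method, so this is not a detail merely left to the SAP. An SAP that followed 7.1 on scores would test an outcome the trial was not sized for, and an SAP that used a test of proportions would depart from the only efficacy method the protocol states.

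At stake is which p-value is the primary one. The primary objective (2.3.1) is worded in terms of VAS, ODI and SF-36. The sentence can therefore be read as a t test on VAS, on ODI, or on the 0/1 responder variable, and nothing in section 7 settles which. These analyses can disagree.

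**Working it through.** **1. The sample size is for proportions.** Inputs from section 7: p1 = 0.30, p2 = 0.68, difference 0.38, mean proportion 0.49, power 80%, alpha 5%, ratio 1:1. Pooled two-proportion formula without continuity correction:

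n per arm = [z(alpha)·√(2·0.49·0.51) + z(0.80)·√(0.30·0.70 + 0.68·0.32)]² / 0.38²

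- Two-sided 5%: (1.960·0.7070 + 0.8416·0.6539)² / 0.1444 = 25.96, so 26 before any allowance for losses.
- One-sided 5%: (1.645·0.7070 + 0.8416·0.6539)² / 0.1444 = 20.33, so 21. The 20% allowance makes this 27 (21/0.8 = 26.25) or 26 (21·1.2 = 25.2, rounded up).

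The stated 26 is thus recovered from proportions in either way. It cannot be recovered from a comparison of means, because no mean difference or SD is given.

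**2. Reading A: section 7.1 applies to the 0/1 responder variable.** For 0/1 data with N patients in two equal arms, the pooled t statistic and the uncorrected chi-square are linked by

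t² = (N − 2)·χ² / (N − χ²).

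With N = 52, the two-sided 5% critical value is t = 2.0086 on 50 degrees of freedom (t² = 4.034). This corresponds to χ² = 52·4.034 / (50 + 4.034) = 3.882, against 3.841 for the chi-square itself. With 26 per arm no table gives a χ² between those limits: the attainable values step from 3.820 to 3.900. The rejection regions are therefore identical.

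Exact binomial enumeration, two-sided 5%, 30% v 68%:

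| Analysed per arm | t test on 0/1: power | Chi-square: power | t test: size at 30% | Chi-square: size at 30% |
|---|---|---|---|---|
| 26 | 78.5% | 78.5% | 5.5% | 5.5% |
| 21 | 69.6% | 70.0% | 4.7% | 5.6% |
| 20 | 66.5% | 66.5% | 5.3% | 5.3% |

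On this reading nothing material changes numerically.

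**3. Reading B: section 7.1 applies to scores.** Assumption, not in the protocol: improvement is one normally distributed score with equal variance in both arms, and a responder is a patient above a fixed cut. Rates of 30% and 68% then imply a shift of z(0.68) + z(0.70) = 0.468 + 0.524 = 0.992 SD. Simulation, two-sided 5%, all patients analysed:

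| Per arm | t test on score | Responder chi-square | Verdicts differ |
|---|---|---|---|
| 26 | 94% | 79% | about 17% |
| 21 | 88% | 70% | about 21% |

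With no true effect at 26 per arm, the score test rejects in about 5.0% and the responder test in about 5.5%. At least one of them rejects in about 8.4%.

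**4. How far this depends on the model.** The endpoint is VAS or ODI, not one score. If two normal scales with equal shifts and correlation 0.3 to 0.7 (assumed) are calibrated so that response on either gives 30% and 68%, a VAS t test at 26 per arm has 87–91% power instead of 94%, and the verdicts differ in 17–20% of trials. The disagreement persists; the 94% does not carry over.

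**The case against.** The strongest case against is that 7.1 is a generic sentence. It mentions neither the primary endpoint nor responders, and it can be read as covering the continuous outcomes in the objective and in 2.4.2, for which the methods fit. The responder test would then simply be unnamed, which a protocol may leave to the SAP. The endpoint itself is fixed as responder status in 2.4.1 and 4.1 and is powered as such, and the worst-case scenario in 7.2 presupposes a responder comparison between arms.

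Much of this stands, and it rules out two stronger readings that a reader might infer:

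- **That the protocol prescribes the wrong test for its primary endpoint.** Section 7.1 does not say it applies to that endpoint. If it does, the t test on 0/1 data at 26 per arm gives the same decisions as the chi-square.
- **That the sponsor is free to choose the primary result, with false-positive risk inflated accordingly.** The endpoint definitions point to responders, and no rule allows the better of two tests to be picked. The 8.4% shows what would follow if either could count; it is not the trial's error rate.

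The objection does not remove the point. Section 7.1 is the only efficacy method stated for the treatment effect, only imputation rules are expressly deferred, and no part of section 7 says how responder proportions are to be compared or estimated.

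**Conclusion.** The point holds as a badly fixed method. The endpoint, sample size and worst-case analysis concern responders; the single stated analysis is one for means and names no outcome; no test or effect estimate for proportions appears. The consequence is an undetermined primary test. That part rests on the text alone.

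The size depends on the reading. It is nil in practice if the t test is run on the 0/1 variable at 26 per arm. If it is run on scores, the verdict differs from the responder test in about 17% of trials under the single-normal-score assumption (about 21% at 21 per arm). These percentages are illustrative: they assume normality, a two-sided 5% level, the planned 30% and 68%, and complete data in the stated number per arm.

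**What to change.** Rewrite section 7.1 to state:

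1. **Primary analysis.** Month-24 responder proportions, cells minus sham, reported as a risk difference with a 95% CI and a test of proportions stratified by the rehabilitation factor used in randomisation (section 2.2), for example Mantel-Haenszel. Adjustment for baseline VAS and ODI is optional. At the planned rates 52 patients give about 25 responders (26·0.30 + 26·0.68 = 25.5), so a fuller logistic model should not be required.
2. **Level.** Say whether the 5% is one- or two-sided. Section 7 does not, and step 1 above shows that 26 per group fits either choice, with different room for losses.
3. **Responder definition.** Sections 2.4.1 and 4.1 differ on the VAS component and must be reconciled into one definition; otherwise the rewritten analysis still cannot be carried out.
4. **Scope of ANOVA and t tests.** Restrict them to the continuous secondary outcomes.

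The cost is protocol and SAP wording, settled before unblinding. No new data are needed.
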